### Outcomes

2.1

This cross-sectional study explores the relationship between oral microbiota composition, immune function, and physical activity levels in young, healthy individuals. The primary objective is to identify microbial and immunological oral signatures associated with varying levels of endurance activity. The microbial targets include a panel of commensal and pathogenic bacterial species, as well as human herpesviruses. By profiling the oral microbiota and salivary immune markers across a spectrum of physical activity, from sedentary to highly active individuals, we seek to identify potential microbial and immunological biomarkers associated with physical activity levels. All targeted microorganisms, cytokines, and recorded parameters are summarized in Table 1.

**Table 1 T1:** Study outcomes.

Principal study endpoints			
Commensal Bacteria	Pathogenic Bacteria	Human Herpes Viruses	Inflammatory Cytokines
*Streptococcus oralis*	*Porphyromonas gingivalis,*	HSV-1,	IFN-*γ*,
*Streptococcus gordonii*	*Streptococcus mutans,*	HSV-2,	IL-1β,
*Streptococcus salivarius,*	*Aggregatibacter*	EBV,	IL-2,
*Streptococcus sanguinis,*	*actinomycetemcomitans,*	CMV,	IL-4,
*Gemella haemolysans,*	*Corynebacterium matruchotii,*	VZV,	IL-6,
*Capnocytophaga gingivalis,*	*Fusobacterium nucleatum,*	HHV-6a,	IL-10,
*Micrococcus luteus,*	*Tannerella forsythia,*	HHV-6b,	IL-12p70,
*Rothia mucilaginosa,*	*Dialister pneumosintes,*	HHV-7,	IL-17A,
*Actinomyces naeslundii,*	*Filifactor alocis,*	HHV-8	TNF-α
*Granulicatella adiacens,*	*Treponema denticola,*		
*Veillonella parvula,*	*Prevotella intermedia,*		
*Eikenella corrodens,*	*Prevotella denticola,*		
*Actinomyces massiliensis*	*Prevotella melaninogenica,*		
	*Prevotella nigrescens,*		
	*Centipeda periodontii,*		
	*Campylobacter rectus,*		
	*Klebsiella pneumoniae,*		
	*Selenomonas sputigena,*		
	*Pseudomonas aeruginosa,*		
	*Haemophilus parainfluenzae,*		
	*Peptostreptococcus anaerobius,*		
	*Eubacterium nodatum,*		
	*Propionibacterium propionicum,*		
	*Parvimonas micra,*		
	*Megasphaera micronuciformis,*		
	*Porphyromonas endodontalis*		
Secondary study endpoints			
Caries	Gingival status	Tooth wear	Extra
• DMF index (WHO criteria)	• Loe and Silness Index (LSI)	• Absence	• Orthodontic retainer
• ICDAS system	• Plaque Index (PI)	• Presence	• MIH
	• Gingival recession (Miller)		• Fluorosis
			• Trauma
			• Tartar
Other study parameters			
• Socio-demographic factors			
• Salivary flow			
• Sport habits			
• Diet			

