### Study design and study population characteristics

2.2

ORASPORT is a single-center, cross-sectional, prospective pilot study. A total of 200 participants aged 18 to 30 years will be enrolled over a 30-month period.

Participants will be primarily recruited from the Sports and Dental Departments of Côte d'Azur University (France), as well as through local sports competitions. Additional recruitments will take place through researcher networks, university posters, and social media platforms. The inclusion criteria are: (i) age between 18 and 30 years old, (ii) male or female, and (iii) if practicing a physical activity, the primary sport must be an endurance activity (i.e., cycling or running).

Participants (*n* = 200) will be classified into three groups according to their physical activity levels: (i) Group 1 (*n* = 50): participants who do not meet the WHO recommendations, (ii) Group 2 (*n* = 100): participants who meet the WHO recommendations, defined as engaging in 150 to 300 min per week of moderate-intensity physical activity, or 75 to 150 min per week of vigorous-intensity physical activity, and (iii) Group 3 (*n* = 50): participants who exceeded the WHO recommendations. The larger size of Group 2 was chosen to account for the expected higher heterogeneity among participants meeting the WHO recommendations compared with those not meeting or exceeding them. The sex of the participants will be balanced as much as possible across the three groups during recruitment to account for potential differences in oral microbiota composition and immune profiles between men and women.

The sample size was not determined through a formal power calculation, as this is an exploratory pilot study designed to generate preliminary data and refine the methodology for a future large-scale investigation. Instead, the proposed sample size was estimated based on feasibility considerations. This number was deemed sufficient to capture variability within and between groups while remaining achievable within the study period. The results from this pilot study will inform the sample size calculation and group allocation strategy for subsequent confirmatory studies.

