### Data visualization and analysis

2.6

The study will generate primarily quantitative data, including the abundance of each microorganism in saliva and mucosal samples, salivary inflammatory markers, oral health parameters (e.g., number of teeth, caries index, plaque index, gingival index, periodontal index), and variables derived from graded scoring system used to interpret data from health questionnaires. Data will be analyzed individually and compared across the three groups, classified according to their level of physical activity. The methodology is based on the development of an account matrix and the implementation of a relational database management system (RedCap™).

Descriptive statics will first summarize participant demographics and distributions. Univariate analysis will then be conducted using standard statistical tests appropriate for each variable (e.g., Student's t-test or Mann–Whitney *U*-test for continuous variables, ANOVA or Kruskal–Wallis for multiple-group comparisons, Chi-square tests for categorical variables, Pearson or Spearman correlation analysis).

To explore complex interactions between oral microbiota, immune markers, and clinical oral heath profiles, multivariate analysis such as principal component analysis (PCA) will be conducted. Subgroup comparisons based on qualitative criteria from self-reported questionnaires (e.g., dietary habits, smoking status) may also be considered. Potential confounding factors, including age, sex, smoking status, diet, and oral hygiene practices, will be accounted for using multivariate linear or logistic regression models, with covariates selected based on theoretical relevance and results from univariate analysis. This strategy ensures that observed associations reflect true relationships rather than confounded effects. Statistical significance will be set at *p* < 0.05.

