The lack of robust and validated biomarkers is particularly striking within the broader context of predictive genomics and personalized medicine. Biomarkers are measurable biological parameters associated with physiological or pathological processes (45). This study offers several notable strengths. It employs cutting-edge high-throughput molecular technologies to investigate both the oral microbiome and the immune system. A major technological innovation lies in the use of high-throughput microfluidic real-time PCR (Biomark HD™ system), which enables the simultaneous detection and quantification of up to 9,216 qPCR reactions in a single run. This platform allows parallel analysis of 96 biological samples across 48 microbiological targets in duplicate, combining high analytical efficiency with an optimized cost-to-performance ratio. Accordingly, a targeted panel of 48 microorganisms (bacteria and viruses) was selected based on recent literature and Socransky's bacterial complexes. This panel includes both commensal bacteria, indicative of oral health, and periodontopathogenic bacteria, associated with gingivitis and periodontitis. In addition to bacterial targets, 9 human herpesviruses were included in the panel, based on the growing evidence supporting the viral–bacterial synergy theory proposed by Slots (46). This concept suggests that herpesviruses may act as cofactors in the pathogenesis of periodontal diseases by modulating host immune responses and enhancing bacterial virulence. Recent studies have demonstrated potential associations between these viruses and the progression of periodontitis, further supporting their inclusion in the present analysis (47). Moreover, the characterization of salivary cytokines and immunoglobulins is performed using a multiplex electrochemiluminescence immunoassay (Meso Scale Discovery®, MSD), which enables the simultaneous quantification of up to 9 immune markers, in duplicate, across 40 samples per run. The S-PLEX® Proinflammatory Panel 1 (Human) was chosen for its high sensitivity in the femtogram range and a broad dynamic detection range. This panel includes cytokines representing both regulatory and pro-inflammatory pathways, allowing a balanced assessment of participants' overall immunological status.

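### About 103 co-equal principal comparisons are read against a single p < 0.05 with no multiplicity control named: about five false positives are expected if activity has no effect

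*Protocol article*

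**What the plan says.** Section 2.1 sets a selection task as the main aim: "The primary objective is to identify microbial and immunological oral signatures associated with varying levels of endurance activity". Table 1 puts every target under one heading, "Principal study endpoints", in four columns: commensal bacteria, pathogenic bacteria, human herpesviruses and inflammatory cytokines. No target is placed above another.

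Section 2.6 names as data "the abundance of each microorganism in saliva and mucosal samples, salivary inflammatory markers", so each microbe yields two measurements per participant. It then says that variables are analysed one at a time and compared across the three activity groups. It lists candidate univariate tests, PCA and covariate-adjusted regression, and ends with the only decision rule in the article: "Statistical significance will be set at *p* < 0.05".

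Section 2.2 calls the study an exploratory pilot with a feasibility-based sample of 200 (50, 100 and 50). On later use it says: "The results from this pilot study will inform the sample size calculation". The Discussion asks for caution in interpretation and leaves validation of candidate biomarkers to larger cohorts.

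**The concern.** Whether a marker is called part of a signature depends on the significance rule. A 5% level per test suits one pre-named endpoint. Across a hundred endpoints of equal rank, it yields several apparent associations even when there are none. The article's safeguard is covariate adjustment, which deals with confounding and does nothing about chance.

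Two uses of the results are exposed. One is the list of candidate markers carried forward. The other is the planning of the next study: effects picked because they crossed a threshold tend to overstate the true effect, so a follow-up sized on them without correction would tend to be too small.

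**Working it through.** The article gives no power, family-wise error or false-positive figure, so there is no calculation of its own to reproduce.

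**Inputs**
- Table 1, by count: 13 commensal bacteria, 25 pathogenic bacteria, 9 herpesviruses and 9 cytokines. Microbes: 13 + 25 + 9 = 47.
- The Discussion gives one more: "a targeted panel of 48 microorganisms (bacteria and viruses) was selected". Both counts are carried below.
- Specimens: two for the microbes (saliva and swab), saliva only for the cytokines (sections 2.3.3 and 2.6).
- Level: 0.05 (section 2.6).
- Unit counted: one overall three-group test per endpoint and specimen. This is the smallest count that covers what section 2.6 describes.

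**Expected false positives if activity has no effect on any endpoint** (number of tests x 0.05; holds whatever the correlation)
- Both specimens: 47 x 2 + 9 = 103 tests; 103 x 0.05 = 5.15.
- With 48 microbes: 48 x 2 + 9 = 105 tests; 105 x 0.05 = 5.25. The discrepancy of one target does not matter here.
- One specimen only: 47 + 9 = 56 tests; 56 x 0.05 = 2.8.

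**Chance of at least one false positive**
- Independent tests: 1 - 0.95^103 = 0.995 (103 tests) and 1 - 0.95^56 = 0.943 (56 tests).
- The tests are unlikely to be independent, since the same microbes are measured twice in each mouth and the cytokines share one saliva sample. For 103 two-sided normal test statistics with an assumed common correlation, the chance is about 95% at 0.3, 78% at 0.5 and 50% at 0.7. The expected count stays at 5.15; correlation makes the false positives arrive in clusters.

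**Rarely detected targets.** Section 2.5 treats a Cq of 35 or more as negative. Targets negative in most participants give conservative tests, so the realised count may fall somewhat below five. The article gives no detection rates from which to say by how much.

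**Price of a stricter rule** (two-sample t-test, Group 1 v Group 3, 50 v 50, 80% power, two-sided)
- Level 0.05: detectable standardised difference d = 0.57.
- Level 0.05/103 = 0.000485: d = 0.89. This is the strictest threshold that Benjamini-Hochberg can impose over 103 tests, so 0.89 is an upper bound.

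**The case against.** The strongest reply is that the article never says its p-values are unadjusted. The same sentence could set the level for adjusted p-values, and a multiplicity procedure is the kind of detail a condensed article leaves to the full protocol or analysis plan. A reader might infer that the sponsor has decided against adjustment. The documents do not show that; they show a single threshold and no procedure. What remains is that the article does fix both the co-equal endpoints and the rule, and those two together produce the count above.

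The second reply is that this is a declared exploratory pilot with validation to follow. That stands, and it lowers the severity. It does not remove the point, because the main aim is itself selection and the results are meant to inform the next sample size. False discovery rate control is designed for this kind of screen.

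Several stronger readings are not supported:
- **That most hits would be chance, or that the rule cannot tell a signature from noise.** This depends on how many real effects exist, which is not stated. For illustration, with 103 endpoints compared at 50 v 50: if 20% truly differ by d = 0.5 (power 0.70), about 14 true and 4 false hits are expected, 22% false. If 10% differ by d = 0.3 (power 0.32), about 3 true and 5 false are expected, 59% false.
- **That the true count is in the hundreds.** Three pairwise contrasts per endpoint would make 309 tests, and all microbe-by-cytokine correlations in one specimen 423. Section 2.6 gives its tests as examples and makes subgroup comparisons optional; it commits to neither total.
- **A specific shortfall in the follow-up study.** At 50 v 50, a true d of 0.3 averages about 0.53 among significant results, but a true d of 0.5 averages only about 0.61. Section 2.2 says only that results will inform the sample size, so the direction of the bias is clear but its size is not.

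**Conclusion.** The point holds as a should-fix. As published, the plan implies about 103 principal tests at 0.05 and about five expected false positives if activity has no effect (2.8 if only one specimen is used). That expectation rests on one overall test per endpoint and specimen, on tests that hold their nominal level, and on reading the stated threshold as applying to each test; it does not need independence. The 99.5% chance of at least one does need independence and should be quoted with the lower values under correlation. The exploratory label makes the consequences milder, but it does not limit how many chance findings enter the signature or feed into the next study's planning.

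**What to change.** Before the data are analysed:

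1. Declare the primary family: one overall three-group test for each microbe in each specimen, plus one for each cytokine. State whether the panel has 47 or 48 microbes.
2. Replace the flat threshold with Benjamini-Hochberg false discovery rate control at 5% across that family, and report q-values beside the estimates.
3. Report pairwise, subgroup, correlation and secondary (dental) results as exploratory estimates with confidence intervals.
4. State that effects selected by significance are inflated and should not be used uncorrected to size the follow-up study.

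If an unpublished analysis plan already does this, a sentence in section 2.6 saying so is enough.

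The cost is wording and a few lines of code, with no new data or visits. The real downside is power per marker: at 50 v 50 and 80% power, the detectable d rises from 0.57 to at most about 0.89, and by less when several markers show real differences. Section 5.4 expects inclusion to end on April 15, 2026. The rule should be settled before results are seen, because a later change would be hard to defend.

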## Discussion

3

This study is based on the premise that oral health reflects overall systemic health. It specifically hypothesizes that regular physical activity, widely recognized for its profound effects on physiological functions, may lead to measurable changes in the balance of the oral ecosystem. While the impact of physical activity on both oral health and athletic performance are well documented (42–44), the influence of exercise on the oral microbiota remains poorly characterized (34). To our knowledge, this study is the first to systematically explore the effects of physical activity on oral health, oral microbiota, and immune response.

The lack of robust and validated biomarkers is particularly striking within the broader context of predictive genomics and personalized medicine. Biomarkers are measurable biological parameters associated with physiological or pathological processes (45). This study offers several notable strengths. It employs cutting-edge high-throughput molecular technologies to investigate both the oral microbiome and the immune system. A major technological innovation lies in the use of high-throughput microfluidic real-time PCR (Biomark HD™ system), which enables the simultaneous detection and quantification of up to 9,216 qPCR reactions in a single run. This platform allows parallel analysis of 96 biological samples across 48 microbiological targets in duplicate, combining high analytical efficiency with an optimized cost-to-performance ratio. Accordingly, a targeted panel of 48 microorganisms (bacteria and viruses) was selected based on recent literature and Socransky's bacterial complexes. This panel includes both commensal bacteria, indicative of oral health, and periodontopathogenic bacteria, associated with gingivitis and periodontitis. In addition to bacterial targets, 9 human herpesviruses were included in the panel, based on the growing evidence supporting the viral–bacterial synergy theory proposed by Slots (46). This concept suggests that herpesviruses may act as cofactors in the pathogenesis of periodontal diseases by modulating host immune responses and enhancing bacterial virulence. Recent studies have demonstrated potential associations between these viruses and the progression of periodontitis, further supporting their inclusion in the present analysis (47). Moreover, the characterization of salivary cytokines and immunoglobulins is performed using a multiplex electrochemiluminescence immunoassay (Meso Scale Discovery®, MSD), which enables the simultaneous quantification of up to 9 immune markers, in duplicate, across 40 samples per run. The S-PLEX® Proinflammatory Panel 1 (Human) was chosen for its high sensitivity in the femtogram range and a broad dynamic detection range. This panel includes cytokines representing both regulatory and pro-inflammatory pathways, allowing a balanced assessment of participants' overall immunological status.

This study also provides a unique opportunity to investigate the impact of physical activity on oral health in young adults with no underlying medical conditions. To our knowledge, it is the first to systematically examine how different levels of physical activity influence key oral health parameters, through the comparison of distinct groups within a large, well-defined cohort.

Several confounding factors, including dietary habits, oral hygiene practices, and psychological stress, are considered in the study to minimize bias in the observed associations. The questionnaire used represents a key strength, as it captures a wide range of lifestyle variables, including assessments of diet, sports-related nutritional supplementation, stress levels, and oral health behaviors. The questionnaire's structure, which combines self-administered validated items, reinforces the reliability and validity of the collected data. Overall, the methodological rigor and scientific relevance of the approach contribute to the robustness and interpretability of the findings. However, this pilot study also presents several limitations. As an exploratory investigation involving a relatively small sample size, its findings must be interpreted with caution. Due to the absence of prior studies on this specific research question, a robust sample size calculation was not feasible at the study's outset. Follow-up studies will therefore be required to establish reproducible, standardized assays and to validate candidate biomarkers in larger, prospective cohorts. Another limitation concerns the narrow age range of participants (18–30 years), which was intentionally selected to reduce age-related variability in oral microbiota composition. Furthermore, the study is limited to endurance sports. Other types of physical activity may exert distinct influences on the oral microbiota. For instance, the use of mouthguards in contact sports, such as boxing, or exposure to chlorinated water in aquatic disciplines, could introduce confounding variables affecting microbial profiles (48–50).

Ultimately, the identification of reliable biomarkers could significantly improve individualized health monitoring in both athletic and sedentary populations, enabling earlier detection of physiological disturbances and enabling the implementation of targeted, personalized health recommendations.

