#### Oral sampling

2.3.3

Saliva samples will be collected immediately following the oral health examination. Participants will be instructed to refrain from eating, drinking (including water), toothbrushing, or smoking for at least 30 min before sampling. An unstimulated whole saliva sample (2 mL) will be obtained via passive drooling (spit method) into sterile tubes. Additionally, a mucosal smear will be collected by swabbing the junction between the tooth and gingiva in the mandibular region using a sterile swab.

All biological samples will be transported to the MICORALIS Laboratory for processing and storage. Each saliva sample will be divided into two 1 mL aliquots. The first aliquots, intended for microbiological analysis, will be mixed with a virus-inactivating and nucleic acid-stabilizing buffer and stored at room temperature until DNA extraction. Extracted DNA will then be stored at −20 °C prior to high-throughput quantitative PCR analysis using the Biomark HD™ system. The second aliquot, intended for immunological analysis, will be treated with protease inhibitors (Pierce™ Protease Inhibitor Tablets, Thermo Scientific™) and immediately stored at −80 °C until cytokine quantification is performed using Meso Scale Discovery® (MSD) multiplex immunoassay technology. Gingival swabs will be stored at 4 °C for a maximum of 24 h or directly frozen at −20 °C to preserve DNA integrity and minimize nuclease activity or microbial overgrowth.

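### The 200 saliva samples need at least five cytokine runs, and no named test or covariate is a plate term; balancing groups over plates and adding plate would be an almost free improvement

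*Protocol article*

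**What the plan says.** - **Endpoints.** Table 1 (section 2.1) lists nine cytokines among the principal endpoints.
- **Sample size.** Section 2.2 states: "A total of 200 participants aged 18 to 30 years will be enrolled over a 30-month period". The participants "will be classified into three groups according to their physical activity levels", with planned sizes of 50, 100 and 50. Each attends one visit (section 2.3) and gives one saliva aliquot for immunology (section 2.3.3).
- **Assay capacity.** The Discussion says the immunoassay "enables the simultaneous quantification of up to 9 immune markers, in duplicate, across 40 samples per run".
- **Timing.** Section 2.3.3 keeps the immunology aliquot at −80 °C "until cytokine quantification is performed using Meso Scale Discovery". It gives no order in which samples are assayed.
- **Calibration.** Section 2.4 includes calibrators in the assay procedure.
- **Analysis.** Section 2.6 states: "Data will be analyzed individually and compared across the three groups, classified according to their level of physical activity". The example tests are the t-test or Mann–Whitney, ANOVA or Kruskal–Wallis, chi-square and correlation. Regression models follow. Their confounders are said to include age, sex, smoking, diet and oral hygiene, chosen on theoretical relevance and univariate results. The section then asserts that this strategy guarantees associations free of confounding.

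**The concern.** Samples read on the same plate share that plate's calibration and handling, so some of the spread in cytokine values is spread between plates. Two things can follow if the analysis ignores plate.

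- **Power.** Where the groups are spread evenly, plate variance stays in the error term and blurs real group differences.
- **False positives.** Where the group mix differs strongly between plates, a plate difference becomes a group difference and can be read as an immune signature of activity.

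The second is conceivable here. Inclusion runs from February 2023 to April 2026 (section 5.4), and recruitment uses several channels, including sports competitions (section 2.2). If plates were filled in order of inclusion, the group mix on each plate would be whatever recruitment delivered in that period. Every covariate named in section 2.6 is a participant characteristic, so the section's assurance about confounding does not reach assay batch.

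**Working it through.** The article states no plate count, power or cytokine SD, so there is no figure of its own to reproduce.

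**1. Number of plates.** Taking one run as one plate, 200/40 = 5, exactly filled. This is a minimum, because any repeat needs a further run. An even spread is 50/5, 100/5, 50/5 = 10/20/10 per plate.

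**2. Model for the consequence (assumed).** Value = within-plate N(0, 1) + plate N(0, τ²) + group effect. The test is the three-group F test at 0.05, with and without plate as a factor. Assumed τ is 0.2, 0.3 or 0.5 of the within-plate SD. The plate share of variance is τ²/(1 + τ²):
- 0.04/1.04 = 4%
- 0.09/1.09 = 8%
- 0.25/1.25 = 20%

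**3. Reference power without plate differences.** For a linear trend of 0, 0.25 and 0.5 SD over Groups 1 to 3, the mean is 0.25 and the noncentrality is 50 × 0.25² + 100 × 0² + 50 × 0.25² = 6.25. On 2 and 197 df this gives power of about 60%.

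**4. Power with balanced plates (10/20/10).** If plate is left out, the noncentrality falls to roughly 6.25/(1 + τ²).
- τ = 0.2: 6.25/1.04 = 6.01, power about 58%, a loss of about 2 points.
- τ = 0.3, simulated: 56.0% without plate, 59.5% with it.
- τ = 0.5, simulated: 49.0% without, 58.4% with, a loss of about 9 to 10 points.

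**5. Power with samples in random order, simulated.**
- τ = 0.3: 56.8% without plate, 59.1% with it.
- τ = 0.5: 52.8% without, 59.2% with.
- At τ = 0.2 the loss is about 1 point.

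**6. Type I error without a plate term, simulated.**

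| Layout | τ = 0.2 | τ = 0.3 | τ = 0.5 |
|---|---|---|---|
| Mild drift (14/20/6 on plate 1 to 6/20/14 on plate 5) | 0.052 | 0.048 | 0.055 |
| Strong drift (20/20/0 on plate 1 to 0/20/20 on plate 5) | 0.073 | 0.106 | 0.192 |
| Strong drift, plate term added | 0.051 | 0.046 | 0.046 |

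Random order stays at about 0.05. Balanced plates analysed without plate fall slightly below it. Repeat simulations of the strong drift gave up to 0.199 at τ = 0.5.

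**7. Adjustment after a strong drift.** The plate term restores the error rate, but power falls to about 47%, because group and plate then overlap. Layout and analysis are therefore both needed.

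**8. A second effect pattern.** With a 0.5 SD shift in Group 3 only, balanced plates at a 20% plate share give 70.8% power without plate and 78.6% with it (7.8 points). In random order the figures are 70.4% and 78.0% (7.6 points). The size is similar.

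**The case against.** **The article is silent rather than wrong.** Plate maps, well order and batch terms often sit in a laboratory procedure or analysis plan, neither of which is shown. The sentence on assay capacity contains no error, and no passage says that plates are filled in order of inclusion. This stands, and it keeps the point at the level of an improvement. It does not remove the point, because section 2.6 does name tests and covariates and does claim that they deal with confounding. A plate map held elsewhere would not put plate into those tests.

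**A plate term is not excluded.** The tests are given as examples, and theoretical relevance could admit plate as a covariate. This stands too. A reader might infer that the plan treats all 200 values as one run or rules out batch adjustment; section 2.6 says neither.

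**Serious inflation needs an unlikely layout.** The 7 to 20% figures need a first plate with no Group 3 samples and a last plate with no Group 1 samples. Nothing in the article shows such a drift. A reader might infer that the plan as written produces false activity effects; the documents do not support that.

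**Calibrators reduce plate differences.** They do, though section 2.4 does not say that they remove them. It might also be inferred that all nine cytokines would move together with the plate. The calculations use a single outcome and do not show this.

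**It is an exploratory pilot without a power target.** True, so a few points of power change no stated decision. The remedy, however, costs almost nothing.

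**Conclusion.** The point holds as an optional, nearly free improvement. The article's own figures require at least five cytokine runs, no named test or covariate is a plate term, and the assurance in section 2.6 does not cover assay batch.

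The size rests on an assumed plate SD of 0.2 to 0.5 of the within-plate SD and, for power, on a trend of 0.5 SD between Groups 1 and 3:
- random order: no inflation, about 1 to 7 points of power lost without a plate term;
- mild drift: no inflation;
- balanced plates: about 2 to 10 points lost without a plate term;
- strong drift: type I error of about 7 to 20%.

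The documents give neither the layout nor the plate SD. They therefore support saying that plate differences can cost power or imitate an activity effect, and not that they will.

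**What to change.** - **Layout.** Samples wait frozen and activity group comes from the visit questionnaire, so the order of assay can be chosen. Spread the three groups over the plates in proportion to their size, about 10/20/10 per plate as far as usable samples and repeats allow, with random well order.
- **Analysis.** Include plate as a factor in each cytokine comparison: two-way ANOVA or regression with plate, or a plate-stratified rank test (van Elteren type) in place of the plain rank tests.
- **Text.** Name plate among the covariates in section 2.6 for the cytokines, and limit the sentence on confounding to the factors actually adjusted for.
- **If some plates have already been run.** Include plate all the same and balance the remaining ones.

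**Cost.** A plate map and four degrees of freedom: the residual falls from 200 − 3 = 197 to 197 − 4 = 193 with five plates. No extra samples, plates or staff are needed.
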